#### Analysis

Linear regression models will be used to examine differences in investigate on the HADS. Scores will be entered in a repeated measure design (GLM), and (optional) covariates will be differences at baseline level. Repeated measures with several independent variables will be used to investigate differences in improvement in all secondary outcome measures between groups. The analyses will be performed on a per protocol basis ('completers'), as well as according to the 'intention-to-treat' principle. Trend analyses will also allow 'last observation carried forward' analyses. To assess whether protocol deviations have caused bias, the results of the intention-to-treat analyses will be compared with analyses of the PST group, including the completers.

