## Methods

### Design

A randomized, controlled trial is being carried out to evaluate the effects of PST. At least 160 primary care patients will be included; 80 will receive usual care and PST and 80 will receive usual care only. At baseline, after the intervention and after 3 and 9 months the patients will be asked to fill in a questionnaire, and at baseline and after 9 months they will be asked to cooperate in a (diagnostic) telephonic interview. Primary outcome is the reduction of symptoms, and other outcomes measured are improvement in problem solving skills, psychological and physical well being, daily functioning, social support, coping styles, problem evaluation and health care utilization.

The Medical Ethics Committee of the VU Medical Center in Amsterdam approved the study design.

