### Outcome measures

#### Primary outcome: reduction of symptoms measured with the HADS

The Hospital Anxiety and Depression Scale (HADS, [16]) is used to monitor symptom levels of anxiety and depression in the study population. The questionnaire consists of 14 items to which answers can be given on a 4-point scale (0–3). The HADS is considered to be unbiased by coexisting general medical conditions, and changes in HADS scores can therefore be used to calculate an objective effect size of the treatment provided (calculations described in 'Sample size'). In the Dutch validation of the HADS [16] the primary care patients have a mean of 6.2 (SD 3.8)for anxiety and 3.7(SD 3.4) for depression with a total mean of 9.9 (SD 6.1). Reliability for these patients is a Cronbach's alpha of .82 for the total score. The HADS is found to perform well in assessing the severity of symptoms [17].

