### Power/analysis

Randomization takes place at patient level. To evaluate the effects of the randomization, descriptive statistics will be used to compare the baseline measurements of the two groups. If necessary, differences between baseline variables on relevant characteristics (such as baseline HADS score) will be entered as covariates in the analysis.

To detect a clinically relevant difference between interventions (effect size of 0.4) with the primary outcome measure HADS (power of .90 and an alpha of .05) 130 completers are needed. In both conditions there will be 65 completers. We estimate the drop-out rate to be on 20%, so we therefore need 160 participants. If 20 practices cooperate, we will need to include 8 patients in every practice. We expect a non-response of 50%, so we will need to screen 16 patients in every practice. In a sample of patients with mixed symptoms of anxiety and depression, Cropper et al. [33]observed a mean overall HADS score of 6.25 at baseline. In the Dutch validation [16] the primary care patients have a mean on anxiety of 6.2 (SD 3.8) and 3.7(SD 3.4) for depression with a total mean of 9.9 (SD6.1). We consider a standardized mean difference (SMD) of 0.4 (p = 0,05) on the primary outcome (HADS) to represent a relevant improvement in the PST group versus the usual care group[34].

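### The trial is sized on one HADS difference of 0.4 SD, but the plan names no primary effect in the repeated-measures model and leaves baseline adjustment optional, so the claimed .90 power attaches to no defined test

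*Protocol article*

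**What the plan says.** All references are to the protocol article.

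- **Outcome.** The outcome section is headed "Primary outcome: reduction of symptoms measured with the HADS". It gives no time point. It quotes norms for the total and for both subscales without saying which score is tested.
- **Schedule.** Under Design: "At baseline, after the intervention and after 3 and 9 months the patients will be asked to fill in a questionnaire". That makes one baseline and three follow-up scores.
- **Sizing.** Under Power/analysis: "We consider a standardized mean difference (SMD) of 0.4 (p = 0,05) on the primary outcome (HADS) to represent a relevant improvement", with "power of .90 and an alpha of .05) 130 completers are needed" and "In both conditions there will be 65 completers". The 0.4 is tied to no wave and no model term.
- **Model.** The Analysis section first names linear regression for the HADS and then continues: "Scores will be entered in a repeated measure design (GLM), and (optional) covariates will be differences at baseline level". It does not say whether the test is a group main effect, a group-by-time interaction or a difference at one wave. It also does not say whether baseline is one of the repeated scores.
- **Baseline HADS.** Power/analysis cites it as an example of a characteristic to be added as a covariate if the arms are found to differ. The Analysis section likewise calls covariates optional.

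**The concern.** A sample size is a statement about one test. Here the effect size, power and alpha are given, but the test they belong to is not. A repeated-measures GLM yields several group-related tests, and they differ in what they estimate and in how much information they use. With baseline as one of four waves, the group main effect averages in a wave at which randomization makes the expected difference zero, so 0.4 shrinks to 0.3. The interaction spreads its power over three degrees of freedom and detects any change in the group difference over time. With baseline as a covariate, the group main effect is the adjusted mean follow-up difference, and a sustained 0.4 stays 0.4.

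Two things are at stake. The trial may be analysed with a test that lacks the power claimed for it. And whether the baseline score, probably the strongest predictor of the outcome, enters the model would depend on the data observed.

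**Working it through.** **Inputs from the article:** standardized difference 0.4, alpha .05 (sidedness not stated, two-sided taken), power .90, n = 65 completers per arm, one baseline and three follow-ups.

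**Assumed, because the article gives no figure:** equal variances, compound symmetry with within-patient correlation r, and a difference of 0.4 held at all three follow-ups. The main range is r = 0.5 to 0.7.

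**Step 1: the plan's own figure.** For one unadjusted two-group comparison, n per arm = 2(1.960 + 1.282)²/0.4² = 131.3, so 132 per arm or 264 in total. The stated 130 is a total and does not reproduce. With 65 per arm the noncentrality is 0.4/√(2/65) = 2.28 and power is about 0.62. This is a separate matter, but it is the right benchmark for what follows.

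**Step 2: baseline as one of four waves.**

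*Group main effect.* The difference is (0 + 3 × 0.4)/4 = 0.3. The variance factor is f = (1 + 3r)/4 and the noncentrality is 0.3/√(2f/65).

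*Group-by-time, 3 df.* The differences are 0, 0.4, 0.4, 0.4 with mean 0.3. Their sum of squares is 0.09 + 3 × 0.01 = 0.12. Then λ = (65/2) × 0.12/(1 − r) = 3.9/(1 − r), referred to F with 3 and 384 df.

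**Step 3: baseline as covariate, three follow-ups as the repeated scores.** For the 1-df group effect, f = (1 + 2r)/3 − r² and the noncentrality is 0.4/√(2f/65).

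| Test | r = 0.5 | r = 0.6 | r = 0.7 |
|---|---|---|---|
| Main effect, four waves: f | 0.625 | 0.700 | 0.775 |
| – noncentrality | 2.16 | 2.04 | 1.94 |
| – power | 0.57 | 0.53 | 0.49 |
| Group-by-time, 3 df: λ | 7.8 | 9.75 | 13.0 |
| – power | 0.64 | 0.75 | 0.87 |
| Mean of three follow-ups, baseline-adjusted: f | 0.417 | 0.373 | 0.310 |
| – noncentrality | 3.53 | 3.73 | 4.10 |
| – power | 0.94 | 0.96 | 0.98 |
| Mean of three follow-ups, unadjusted, f = (1 + 2r)/3: power | 0.79 | 0.75 | 0.72 |
| One follow-up, baseline-adjusted, f = 1 − r²: power | 0.74 | 0.81 | 0.89 |
| One follow-up, unadjusted, f = 1: power | 0.62 | 0.62 | 0.62 |

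Adjusting for baseline lifts the power of the follow-up mean from 0.79 to 0.94 at r = 0.5 and from 0.72 to 0.98 at r = 0.7.

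**Step 4: sensitivity to r.** At r = 0.3 the three main candidates give 0.69 (four-wave main effect), 0.48 (interaction) and about 0.93 (adjusted mean). At r = 0.8 they give about 0.45, 0.97 and above 0.99. The order of the first two changes. The adjusted mean stays above .90 throughout.

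**Step 5: sensitivity to a fading effect.** With differences of 0.4, 0.2 and 0 at the three follow-ups, the mean is 0.2, which halves the Step 3 noncentralities: 3.53/2 = 1.77 and 4.10/2 = 2.05. Power falls to about 0.42 (r = 0.5) and 0.53 (r = 0.7). The 3-df interaction then has about 0.60 and 0.83. The advantage of the averaged contrast therefore depends on the benefit lasting.

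**The case against.** The strongest reply is that the article never says baseline is one of the repeated scores. It names baseline HADS as a possible covariate, and on that reading the GLM's group effect is the 1-df contrast with power of 0.94 to 0.98. This stands. A reader might infer that the stated model wastes the follow-up information. The text supports only that it may, because the adjustment is conditional and the tested effect is not named.

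Second, the shortfall is not all due to the model. One unadjusted follow-up with 65 per arm has only about 0.62 power, and the 3-df test at r = 0.5 to 0.7 does at least as well. This also stands: part of the gap comes from the sample-size figure.

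Third, a reader might infer an inflated type I error. Three unadjusted wave-wise tests at .05 would carry a familywise error of about 0.11 to 0.12 at the same correlations, but no passage lets a single wave count as success. The figure is conditional.

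Fourth, a reader might infer that the arms are measured at different times, since the first follow-up is placed after an intervention that only the PST arm receives. The article gives no matching date for usual care, but it does not say that timing differs either. A condensed article may leave that calendar to the full protocol, so confounding with natural recovery is not shown.

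Fifth, the exact model specification is often left to an analysis plan. That is fair for the covariance structure. It is weaker for the effect on which the sample size is stated, which should be identifiable where the power claim is made.

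**Conclusion.** The point holds as an ambiguity with material consequences. The article claims .90 power for a difference of 0.4 without saying which test has that power, and it makes adjustment for baseline HADS depend on observed imbalance. At 65 per arm, power is about 0.49 to 0.87 for the two usual group tests with baseline as a wave, and 0.94 to 0.98 for the baseline-adjusted follow-up mean.

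These figures rest on compound symmetry, r = 0.5 to 0.7 and an effect sustained to 9 months, none of which the article states. The documents do not show that the error rate is inflated or that the arms are measured on different calendars. The point deserves correction but does not invalidate the design.

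**What to change.** Name one primary 1-df contrast on the HADS total (14 items). For example: the difference between arms in mean HADS total over the three follow-ups, from one repeated-measures model with baseline HADS always a covariate whatever the observed imbalance, tested at two-sided .05. Report the wave-specific differences as secondary. Restate the power for that contrast, with the assumed within-patient correlation.

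If one time point is preferred, name it, keep the baseline adjustment and restate the power, which would be about 0.74 to 0.89 at the same correlations with 65 per arm.

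Add one sentence confirming that follow-ups fall at the same time since randomization in both arms, including the questionnaire that follows the intervention. If wave-wise claims are intended, say how multiplicity is handled.

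The cost is analysis wording only, since baseline HADS is already collected. The downside is dilution of the averaged contrast if benefit fades by 9 months. The wave-specific estimates would show this but would not restore the power of the primary test.

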### Strengths and limitations

Many methodological requirements for a high quality trial are met [36]. Allocation is concealed through block-randomization by an external researcher. Recruitment of responders will be in the GP's waiting room, without the GP knowing where and how randomization will take place. The methodology used in this trial will overcome concerns of selection bias. The relevance to the Dutch primary care seems sufficient and the generalisability of our sample to patients in everyday practice seems high. The sample size is large, when compared to other trials on psychological problems in general practice [37]. Additionally, whether the outcome is negative or positive, the project will give a clearer understanding of who might or might not benefit from this treatment.

Another strength of this study is the chosen primary outcome, the self-report HADS. The HADS is a well-known questionnaire to measure reduction of symptoms of anxiety and depression. Many previous trials in psychiatry have relied on assessments of the therapist. Another strength is the combination of quantitative assessments and a qualitative process evaluation. If the psychiatric symptoms decline more in the intervention group than in the usual care group, we can therefore safely attribute this to PST treatment. If not, we will explore mechanisms This will provide useful information about implementing the intervention. A practical strength of the study is that the intervention can take place without disturbing care as usual, both in the study as in future implementation.

Some limitations of the present study need to be addressed. It is possible that patients are less motivated to attend PST treatment since screening of all participants takes place in the waiting room of the GP's. This may be lead to a higher dropout percentage in the PST-condition in comparison with the dropout percentage of the CAU.

This study may be criticized because of the lack of a control group without treatment. However, patients are always free to visit their general practitioners. Furthermore, naturalistic studies of the longitudinal course of anxiety and depression indicate that patients who have these symptoms longer than three months are suffering from chronic symptoms [38,39].

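### Per-protocol and intention-to-treat analyses have equal standing in a superiority trial, so a completer contrast that randomisation does not protect could support the claim of effectiveness

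*Protocol article*

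**What the plan says.** The Analysis section plans two analysis sets side by side: "The analyses will be performed on a per protocol basis ('completers'), as well as according to the 'intention-to-treat' principle". It does not rank them. To judge whether protocol deviations caused bias, it says "the results of the intention-to-treat analyses will be compared with analyses of the PST group, including the completers", with no rule for acting on a difference. The only method it names for incomplete follow-up is optional: "Trend analyses will also allow 'last observation carried forward' analyses".

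The Power/analysis section sizes the trial in the same term: "130 completers are needed". It adds "In both conditions there will be 65 completers" and raises the total to 160 for 20% dropout. The Design section gives 80 patients per arm.

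Strengths and limitations explains why loss might be unequal: "It is possible that patients are less motivated to attend PST treatment", because they were recruited by waiting-room screening. It says this may make dropout higher under PST than under usual care. The same section holds that a larger symptom decline with PST could safely be put down to the treatment, without saying which analysis set would show it.

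**The concern.** The aim is superiority. Completing is an event after randomisation. If less motivated patients leave PST, the PST completers are a selected group, and comparing them with usual-care completers is no longer a randomised comparison. In a superiority trial such selection tends to favour the new treatment when leavers have the poorer outlook.

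With the sets unranked, nothing in the article prevents a favourable completer result beside a null intention-to-treat result from being reported as effectiveness. The article gives protection against selective analysis as a reason for publishing the design, and an unranked pair of analyses leaves that choice open. Two chances of significance would also push the false-positive rate above the stated .05.

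**Working it through.** **1. The plan's own numbers.** 130 / (1 − 0.20) = 162.5, against 160 stated; going back, 160 × 0.80 = 128. The dropout step therefore reproduces to within rounding. Completers per arm are 65 of 80, a loss of 15/80 = 18.75% in *each* arm. (The 130 itself does not reproduce from a plain two-group comparison at effect size 0.4 and power .90, which needs about 132 per arm. That is a separate matter and nothing below depends on it.)

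**2. Bias of a completer contrast.** Let d be the dropout share in an arm and g the outcome gap, in SD, between stayers and leavers. The mean among stayers exceeds the mean of the whole arm by d × g. With no true effect:

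bias = d(PST) × g(PST) − d(UC) × g(UC)

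From the protocol: d = 0.20, and SD 6.1 for the HADS total. Assumed: g(PST) between 0.3 and 0.5, and g(UC) = 0.

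- g = 0.3: 0.20 × 0.3 = 0.06 SD, which is 15% of the 0.4 target, or 0.06 × 6.1 = 0.37 HADS points.
- g = 0.5: 0.20 × 0.5 = 0.10 SD, which is 25% of the target, or 0.61 points.

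**3. Chance of a false finding for PST.** With 64 completers per arm (80 × 0.80), SE = √(1/64 + 1/64) = 0.177 SD. The chance of a significant result in favour of PST is 1 − Φ(1.96 − bias/SE):

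- bias 0.06: 1 − Φ(1.96 − 0.34) = 5.3%
- bias 0.10: 1 − Φ(1.96 − 0.57) = 8.2%

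The nominal value in that direction is 2.5%.

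**4. Two tests, either of which may count.** Suppose there is no selection bias and completers are a fraction f of the full set. The two test statistics then correlate at about √f. For f = 0.80 (correlation 0.894), the two-sided chance that at least one is significant at .05 is 0.071. It is 0.065 at f = 0.90 and 0.076 at f = 0.70.

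**5. What the planned comparison can show.** Let e be the true effect in patients who complete and l the true effect in those who leave. With full outcome data:

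- ITT = (1 − d) × e + d × l
- completer contrast = e + d × g

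Take d = 0.20.

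| Case | e | l | g | ITT | Completers |
|---|---|---|---|---|---|
| Dilution only | 0.40 | 0 | 0 | 0.32 | 0.40 |
| Selection only | 0.32 | 0.32 | 0.40 | 0.32 | 0.32 + 0.08 = 0.40 |

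The two cases give identical results. There are two observed figures and three unknowns, so the comparison reveals a gap of 0.08 SD but not its cause.

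**The case against.** Much can fairly be said for the plan.

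- **Sizing on completers is routine.** Calculating evaluable patients and inflating for dropout is not an error, and the randomised number is given. A reader might infer that the trial was designed around a per-protocol analysis. The documents do not show that; they only use one undefined word for both the sample-size target and the analysis set.
- **The usual-care arm is not nearly unselected.** A reader might infer that only PST loses patients. The Power/analysis section projects equal completers in both arms, and the remark on PST dropout is hedged. If usual-care leavers also did worse, the bias in step 2 would shrink or cancel. If early improvers left PST, it would reverse.
- **A larger bias is not documented.** With 30% PST dropout and a 0.5 SD gap the bias would be 0.15 SD, 38% of the target. The 30% is not in the protocol, so this is no basis for a headline.
- **The bias check is not blind.** With no true effect and full outcome data, intention-to-treat would show 0 while completers showed 0.06 to 0.10 SD. To say that the check cannot detect selection goes too far.
- **No sentence says either set suffices.** The 0.071 depends on a decision rule that the article does not state. The closing sentence of the Analysis section can be read as making intention-to-treat the reference, and an unseen analysis plan may rank the sets.

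These points limit the size and certainty of the concern. They do not remove it. The article does fix its analysis sets, fixes them as a pair, and attaches an unqualified causal conclusion without saying which set must support it.

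**Conclusion.** The point holds in a limited form. The article gives completer and intention-to-treat analyses equal standing in a superiority trial, while anticipating that motivation may drive dropout in one arm. Under the stated assumptions the completer contrast would favour PST by about 0.06 to 0.10 SD with no true effect, and an either-set rule would put two-sided type I error at about 0.07. These figures illustrate the risk and do not predict what this trial will show: the leaver-stayer gap, the uninformative usual-care loss and the either-set rule are all assumed. The planned comparison would signal a difference but could not explain it.

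Calling an analysis intention-to-treat is also not enough. If patients who stop PST also stop returning questionnaires, their outcomes are missing. Comparing simple means of whatever was returned would then carry the same bias as the completer contrast. The only remedy the article names, carrying the last score forward, assumes that scores stay still after dropout.

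**What to change.** Add to the Analysis section wording such as: *The primary conclusion rests on the between-arm comparison of HADS scores in all randomised patients, analysed in the arm to which they were allocated. The per-protocol analysis is supportive and cannot by itself support a claim of effectiveness.*

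In addition:

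- Follow all patients up on the questionnaire schedule whether or not they attend PST.
- For the primary analysis, replace last observation carried forward with a likelihood-based repeated-measures model using every available HADS observation. It relies on loss being explained by observed scores, so follow-up of leavers still matters.
- Define completers: whether the term means completing PST sessions or completing questionnaires, and how it applies to usual care.
- Describe the comparison of the two sets as descriptive. A complier-average analysis is an option for the effect in attenders, but it needs a compliance definition and further assumptions, and does not solve missing outcomes.

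The sample-size paragraph needs no change on this account. The cost is a few sentences, a change of model, and the effort of obtaining questionnaires from patients who stop PST. No additional patients are needed for this change. It does mean accepting a diluted effect: if 20% of the PST arm gained nothing, a true 0.4 would appear as 0.4 × 0.8 = 0.32.

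### With 20% dropout planned, a repeated-measures GLM on completers and last observation carried forward both leave the HADS comparison at risk of bias

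*Protocol article*

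**What the plan says.** HADS is collected at four waves: baseline, after the intervention, and at 3 and 9 months (Protocol article, Design). The Analysis section gives the model: "Scores will be entered in a repeated measure design (GLM), and (optional) covariates will be differences at baseline level". It gives the analysis sets: "The analyses will be performed on a per protocol basis ('completers'), as well as according to the 'intention-to-treat' principle". Neither set is named as primary. On missing scores it adds: "Trend analyses will also allow 'last observation carried forward' analyses". Its one check on bias concerns protocol deviations, and sets the intention-to-treat results against analyses of the PST group that include its completers.

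On dropout, Power/analysis states: "We estimate the drop-out rate to be on 20%, so we therefore need 160 participants", and counts 65 completers in each arm. Strengths and limitations is less sure that the arms will be alike. It says "It is possible that patients are less motivated to attend PST treatment" and continues: "This may be lead to a higher dropout percentage in the PST-condition in comparison with the dropout percentage of the CAU". No dropout rate by arm is given.

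**The concern.** A repeated-measures GLM in its standard form drops any patient with a missing wave. An intention-to-treat version therefore needs values for the missing waves, and LOCF is the only technique the article names for supplying them.

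- **Complete cases** compare patients selected by whether they stayed. If those with more symptoms leave more often, and more of them leave one arm, the remaining groups are no longer comparable.
- **LOCF** freezes a dropout at an earlier score, sometimes baseline, and treats it as a real later observation. This removes any change after that point. If scores fall over time in both arms, the arm with more dropout is penalised.

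The stake is the main conclusion. Strengths and limitations says that a larger symptom decline under PST could safely be attributed to PST. That confidence is not earned if part of the contrast, in either direction, reflects who left and how their scores were filled in.

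**Working it through.** **The plan's own dropout figure.** 130 completers / (1 - 0.20) = 162.5, against 160 stated. In the other direction, 160 x 0.80 = 128 completers, or 64 per arm. The step holds to within 3%. The total does not settle the split between arms, because with 80 randomised per arm these all leave 128 completers:

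- 20% in each arm: 64 + 64
- 25% PST, 15% usual care: 60 + 68
- 30% PST, 10% usual care: 56 + 72

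**Inputs for the illustration.** From the article: overall dropout of 20%, and a target effect of 0.4 SD (Power/analysis). Assumed, because the article gives no value: dropout by arm (pP for PST, pU for usual care), and usual-care improvement c from 0 to 1.0 SD. It is also assumed that every dropout has no score after baseline and would have shared the true effect d = 0.40.

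**LOCF with baseline carried forward.** Only those who stay show change:

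estimate = (c + d)(1 - pP) - c(1 - pU) = d(1 - pP) - c(pP - pU)

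| Dropout PST / usual care | c = 0 | c = 0.3 | c = 0.6 | c = 1.0 |
|---|---|---|---|---|
| 20% / 20% | 0.32 | 0.32 | 0.32 | 0.32 |
| 25% / 15% | 0.30 | 0.27 | 0.24 | 0.20 |
| 30% / 10% | 0.28 | 0.22 | 0.16 | 0.08 |

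For example, the last cell is 0.40 x 0.70 - 1.0 x 0.20 = 0.08. There are two parts. The first, d(1 - pP), loses effect even with equal dropout. The second, c(pP - pU), needs both a time trend and unequal dropout.

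**Dropout spread over the visits.** A simulation with four visits, correlation 0.6 between visits and a true effect of 0.40 gave smaller LOCF losses:

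- LOCF: about 0.37 at 20%/20%, 0.36 to 0.27 at 25%/15%, and 0.35 to 0.18 at 30%/10%, over c from 0 to 1.0 and over random and score-dependent dropout.
- Completers: about 0.40 if dropout is completely at random. If patients with higher scores leave more often, about 0.44 at 25%/15% and up to 0.49 at 30%/10%.

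With a true effect of zero and score-dependent dropout, LOCF ran from 0 to about -0.17 and completers from 0 to about +0.09. The two analyses can therefore err on opposite sides of the truth.

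**Where the bias vanishes.** With d = 0 and c = 0, the formula gives 0 for any dropout split. With random dropout, the completers estimate is also unbiased.

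**If dropouts lose all benefit of PST.** The true intention-to-treat effect is then itself d(1 - pP), which is 0.32 at 20%/20% and 0.28 at 30%/10%. The LOCF error reduces to -c(pP - pU): zero at equal dropout, and 0 to -0.20 at 30%/10%. In this case a completers estimate near 0.40 overstates the effect.

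**The case against.** A reader might infer that the authors expect more dropout under PST, that LOCF is the intention-to-treat rule, and that the effect estimate is therefore biased against PST. The article does not support this.

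- Higher PST dropout is raised as a possibility under limitations. The sample size assumes the same number of completers in each arm.
- LOCF is worded as an additional analysis linked to trend analyses, not as the rule for intention-to-treat. It is also not the only stated approach to dropout, since completers and intention-to-treat sets are both planned and compared.
- The motivation remark concerns attendance at PST. Questionnaires go to all patients, so someone who stops PST may still return a HADS. The article does not separate leaving treatment from leaving the study.
- A fall in scores in both arms is assumed, not stated. Entry is on the GHQ-12 and the outcome is the HADS, which weakens regression to the mean, and the article itself cites evidence that symptoms lasting beyond three months are chronic.
- No software procedure or deletion rule is given for the GLM. Complete-case use is the usual reading, not a stated one.
- A fuller analysis plan could name further methods. Their absence from a condensed article is no finding.

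These objections limit the point to a risk of bias of unknown size. They do not remove it. The criticism is of methods the article does name, under a planned 20% dropout that it states and a possible imbalance that it raises. Its one comparison of analyses asks about protocol deviations. A gap between LOCF and completers would not show which is nearer the truth, and agreement between them would not show that both are right.

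**Conclusion.** The point holds as a risk of bias. The GLM in its standard form, the completers analysis and LOCF are a weak basis for the primary comparison when one patient in five is expected to be lost and the loss may differ by arm. Neither direction nor size can be fixed from the article. For a true effect of 0.40 SD the illustrations run from almost no error to a loss of 0.32 SD (0.40 - 0.08) for LOCF, and from no error to an overstatement of about 0.09 SD for completers. The largest LOCF loss needs 30% against 10% dropout, a 1.0 SD improvement under usual care, every dropout at baseline, and dropouts who would have benefited fully. It marks the edge of the range and is not a forecast. Even equal dropout of 20% costs LOCF 0.08 SD if all carry baseline forward and would have shared the effect, which is 20% of the 0.4 target (0.08 / 0.40).

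**What to change.** 1. Name the intention-to-treat analysis as primary. Fit it as a likelihood-based linear mixed model on all available HADS scores of all randomised patients, with arm, categorical time, arm-by-time, baseline HADS as a fixed covariate, and an unstructured covariance.
2. Drop LOCF, or keep it only as a labelled supplementary analysis. Keep the completers analysis as secondary.
3. Add a multiple-imputation sensitivity analysis that shifts the imputed scores of PST dropouts over a stated range. The mixed model assumes that dropouts would have continued like comparable patients who stayed; the shift tests that. Imputation also brings in patients with a baseline score only, who add nothing to a model with baseline as covariate.

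This needs no new data and no change to conduct. The cost is a change of analysis wording and slightly more complex analysis and reporting.
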